##### Cancer Treatment Cohort

This will take place entirely at the Cancer Diseases Hospital, with some patients being recruited from the University Teaching Hospital. A total of 500 AYA living with HIV who have been diagnosed with CC, NHL, or KS will be recruited into the study, with 50% (250/500) of the patients in each trial arm (ie, one-time educational campaign vs the ARROW intervention). Patients will be surveyed annually at 12, 24, and 36 months. Trained data collectors will obtain consent and enroll AYA living with HIV, aged 15 to 39 years. We will be aiming for the following targets for each cancer type: 50% (250/500) of the participants with CC, 30% (150/500) of the participants with KS, and 20% (100/500) participants with NHL (with an overall equal number of male and female AYA living with HIV for KS and NHL). While AYA living with HIV who are pregnant will be excluded, as they require specialized care, those who become pregnant during the trial period will remain enrolled in the study; CC screening and physical examinations for KS and NHL will be offered based on Zambian guidelines pertaining to pregnancy.

We hypothesize that, by facilitating peer support to address barriers and gaps at multiple levels, the ARROW program will be more effective than the one-time education campaign, but more expensive as well. As shown in Figure 2, we will simultaneously conduct separate randomized controlled trials at the HIV treatment facilities and at the Cancer Diseases Hospital. The trials will be initiated upon completion of the preimplementation preparation activities. We will then embed PCs into the care teams at the HIV facilities and the Cancer Diseases Hospital and initiate the planned implementation activities of the ARROW Provider Network in the ARROW program arm. The comparison arm will receive the one-time education campaign: health care providers at the HIV facilities (particularly physicians and nurses) will receive a brochure with key guidance for early diagnosis of cancers in AYA living with HIV, and the AYA living with HIV upon recruitment will also receive education brochures at both the HIV facilities and the Cancer Diseases Hospital. The Health Care Collaborative will continue to meet as planned on a quarterly basis.

**Figure 2 figure2:**
[figure not shown]
Experimental design and sample sizes. ARROW: AYAHIV Role-Based Responsibilities for Oncology-Focused Workforce; AYA: adolescents and young adults.

#### Study End Points

##### Early Detection Cohort

We will assess effectiveness based on dual primary end points. The first primary end point is the proportion of those who complete a physical examination visit for KS and NHL and the proportion of those who are up to date with CC screening (female participants only) at 12 months. The second primary end point is the proportion of those who complete the recommended follow-up supplemental or diagnostic procedures (within 3 months of receiving follow-up referral), those who initiate cancer treatment (within 3 months of diagnosis), and those who complete additional cancer detection visits over 36 months. The secondary end point, evaluated at 36 months, is the proportion of those diagnosed at an early stage (among those diagnosed with KS, NHL, and CC). We will likely have a few cancer cases in the study facilities. Therefore, these findings will not be conclusive but will offer insights into the potential impact of the ARROW program on facilitating diagnosis at an early stage.

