##### Early Detection Cohort

We propose a cluster randomized study to be implemented at 18 HIV treatment facilities in Lusaka province. Three facilities serving each type of regional population (urban, periurban, or rural populations) will be randomly assigned to a study arm: the ARROW program or one-time education. Overall, 9 (50%) facilities will be assigned to each arm of the trial, with data collection at baseline and at 12-, 24-, and 36-month follow-up. At each of the 18 clinics, we will enroll 100 men and 100 females resulting in a total of 3600 participants in the early detection cohort. The 200 AYA living with HIV per facility will be selected by first reviewing the HIV register and identifying those who meet the study inclusion criteria: 15 to 39 years of age, on ART for at least 6 months, not pregnant, and with no pending plans to move from the current residence during the 3-year study duration. For all the 3600 participants, we will collect baseline data and capture information on study end points from the SmartCare system, and the supplemental data will be collected by PCs and trained study data collectors (eg, tracking referrals for all participants and obtaining results of biopsies).

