#### Sample Size and Recruitment

##### Early Detection Cohort

We will use stratified random sampling to select an equal number of male and female participants and a mix of AYA living with HIV with perinatally and behaviorally acquired HIV. In terms of age distribution, 20% (720/3600) of the sample will be aged 15 to 19 years, 20% (720/3600) will be aged 20 to 24 years, and 60% (2160/3600) will be aged 25 to 39 years. We will oversample AYA living with HIV in each stratum to account for AYA living with HIV who may not meet inclusion criteria or who decline to participate. HIV facility staff will contact AYA living with HIV or consenting adults (for those aged 15 to 17 years) to discuss the study, and those interested will meet with trained data collectors who will assess eligibility and obtain consent or assent. The sample size was calculated assuming conventional specifications (α=.025 for each end point, 2-sided tests) based on the dual primary end points and allowing for the detection of an absolute 20% point improvement in the primary end points, which is our minimum threshold to consider the ARROW program successful. For the one-time education arm, given the current low level of uptake of early diagnosis services, we estimate uptake of physical examinations to be about 15% (15/100) and CC screening to be about 20% (20/100) at 12 months. With our proposed sample size of 3600, we will be able to detect a 20% difference in uptake of physician examination (35% in the ARROW arm) with over 90% power and CC screening (40% in the ARROW arm) with over 85% power. We can achieve this even after accounting for up to 10% attrition at 12 months (a previous study conducted by the research team achieved this retention rate without the level of active participant contact planned for this study) [67]. We estimate that the interclass correlation coefficient will be in the range of 0.03 to 0.05 because correlation coefficients for binary data are typically quite small, especially when physical examinations and screening uptake are very low [68].

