**Data elements for primary, secondary, and tertiary end points: HIV and cancer care continuum**				
	Proportion of participants completing physical examination (KS^a^ and NHL^b^) and up to date with CC^c^ screening	Confirmation of services will be based on clinical records and PC^d^ tracking tool (primary end point at 24 mo)	Biological, imaging, and clinical procedures identified through clinical records and study database	12, 24, and 36 mo
	Proportion of participants completing diagnostic tests and initiating treatment in ≤90 d	Measured as days from referral for testing and cancer diagnosis, respectively; based on chart review and study data	Biological, imaging, and clinical procedures identified through clinical records and study database	24 and 36 mo
	Proportion of participants completing repeat examinations and screening at the recommended interval	Screening every 2 y for CC and annual examination (especially when CD4^e^<100) based on the Zambian guidelines	Biological, imaging, and clinical procedures identified through clinical records and study database	36 mo
	Proportion of participants with early-stage diagnosis^f^	Stage 1 or 2 for NHL and CC; good risk for KS^g^	Biological, imaging, and clinical procedures identified through clinical records and study database	36 mo
	Proportion of participants adherent to cancer treatment^f^	Complete cancer treatment modalities as recommended	Biological, imaging, and clinical procedures identified through clinical records and study database	12 mo after diagnosis
	Proportion of participants alive at 12 mo after diagnosis^f^	Follow-up conducted by PCs and entered in study database	Biological, imaging, and clinical procedures identified through clinical records and study database	12 mo after diagnosis
	Proportion of participants with recurrent disease^f^	AYA^h^ living with HIV and cancer who experience cancer recurrence	Biological, imaging, and clinical procedures identified through clinical records and study database	36 mo
	Proportion of participants adherent to ART^i^ and viral load	Prescription filled every 3 to 6 mo; blood test	Biological, imaging, and clinical procedures identified through clinical records and study database	Annually

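### Read with the article's 2-year interval, 'up to date' at 12 months counts cervical screens done before enrolment; baseline screening status should be a fixed covariate and the 20% v 40% given a stated meaning.

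*Protocol article*

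**What the plan says.** Under Study End Points, Early Detection Cohort, the first primary end point has a physical examination component and a cervical component. The cervical one is a status at a date: "the proportion of those who are up to date with CC screening (female participants only) at 12 months".

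Table 2 gives the only cervical interval in the article, "Screening every 2 y for CC and annual examination". It stands in the row on repeat examinations and screening, not in the row for the primary end point. The primary end point row labels that end point as assessed at 24 months, whereas the end point section says 12.

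Under Sample Size and Recruitment, Early Detection Cohort, the control assumption is "we estimate uptake of physical examinations to be about 15% (15/100) and CC screening to be about 20% (20/100) at 12 months", and the resulting claim is "CC screening (40% in the ARROW arm) with over 85% power". The same paragraph ties the sample size to the dual primary end points and makes 20 percentage points the minimum for calling ARROW a success.

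The inclusion criteria under Overall Study Design cover age, time on ART, pregnancy and plans to move. Earlier cervical screening is not among them. Under Analysis of Hypotheses, baseline covariates enter the model only if descriptive comparison suggests that the arms differ.

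**The concern.** With a 2-year interval, the look-back at month 12 reaches to one year before enrolment. A woman screened in that year is up to date at month 12 by construction. She counts as a success in both arms, and nothing done after enrolment can change that.

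There are two consequences. On the absolute scale, a true 20-point rise in new screening among the remaining women appears as less than 20 points, so the program could miss its own threshold because of screens that preceded it. And fixed successes add variation to the outcome that a baseline variable would explain, but the adjustment rule admits covariates only when the arms look unbalanced. The power paragraph speaks of uptake and does not say whether earlier screens are included, so the reader cannot tell which quantity the 20% and 40% describe.

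**Working it through.** **Inputs from the protocol.** Facilities: "Overall, 9 (50%) facilities will be assigned to each arm of the trial". Women: "At each of the 18 clinics, we will enroll 100 men and 100 females", so 100 women per facility, or m = 90 after "accounting for up to 10% attrition at 12 months". Type I error: "α=.025 for each end point, 2-sided tests". Rates: 20% v 40%. ICC: 0.03 to 0.05.

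**Assumption, not in the protocol.** Carry-over c is the share of women up to date at month 12 through a screen in the year before enrolment. It is equal in both arms and shown from 0 to 20%.

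**Formulas.** Design effect = 1 + (m − 1) × ICC. Effective n per arm = 9m / design effect. SE = √{[p1(1 − p1) + p2(1 − p2)] / effective n}. Normal power = Φ(difference/SE − 2.241). The second version uses a noncentral t with 18 − 2 = 16 df.

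**Step 1: the stated figure.** At ICC 0.05 the design effect is 1 + 89 × 0.05 = 5.45 and effective n is 810/5.45 = 148.6. SE = √(0.40/148.6) = 0.0519 and 0.20/0.0519 = 3.855. Power is Φ(1.614) = 0.947 (t: 0.904). At ICC 0.03 (design effect 3.67, effective n 220.7) it is 0.993 (t: 0.981). The claim of over 85% holds on its own inputs.

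**Step 2: 20% v 40% applies only to women not already covered.** Each arm's rate is c + (1 − c) × uptake, so the difference is 20(1 − c) points.

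| c | Rates | Difference (points) | Power, ICC 0.05: normal (t) | Power, ICC 0.03: normal (t) |
|---|---|---|---|---|
| 0 | 20% v 40% | 20 | 0.947 (0.904) | 0.993 (0.981) |
| 5% | 24% v 43% | 19 | 0.903 (0.845) | 0.981 (0.958) |
| 10% | 28% v 46% | 18 | 0.848 (0.779) | 0.960 (0.922) |
| 20% | 36% v 52% | 16 | 0.717 (0.637) | 0.883 (0.820) |

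Normal power crosses 85% at c of about 10% for ICC 0.05 and about 23% for ICC 0.03. With t on 16 df the crossings are at about 5% and 17.5%.

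**Step 3: the 20-point gap holds across all women.** Rates are c + 20% v c + 40%. At ICC 0.05, power is 0.927 (t: 0.876) at c = 5%, 0.912 (0.856) at 10% and 0.899 (0.840) at 20%. At ICC 0.03 it is 0.955 or higher throughout, by either version.

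**Step 4: 20% and 40% already include earlier screens.** The stated power then stands, but the implied new screening changes. At c = 10% it is (0.20 − 0.10)/0.90 = 11% v (0.40 − 0.10)/0.90 = 33% among uncovered women, a 22-point rise. At c = 20% the control arm would have no new screening.

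**Step 5: what a baseline flag recovers, under the Step 2 model.** Flagged women have no outcome variance, so adjustment lowers the summed variance from p1(1 − p1) + p2(1 − p2) to (1 − c)(0.16 + 0.24). At c = 20% that is 0.48 down to 0.32. With the same design effect at ICC 0.05, SE = √(0.32/148.6) = 0.0464, 0.16/0.0464 = 3.448, and power is Φ(1.207) = 0.886 (t: 0.824). The difference is still 16 points.

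Restricting to uncovered women (m = 72, design effect 4.55, effective n 648/4.55 = 142.4) keeps the full 20 points: SE = √(0.40/142.4) = 0.0530 and power 0.937 (t: 0.890).

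**The case against.** The strongest reply is that the mismatch is inferred. The sample size paragraph says the calculation rests on the primary end points, so 20% can be read as the up-to-date proportion expected in the control arm, with 'uptake' as loose wording. The 2-year interval belongs to another row of Table 2, and a condensed article may leave the working definition of 'up to date' to the full protocol. Even with carry-over, the 20-point gap may have been meant for all women (Step 3), and at ICC 0.03 the normal power stays above 85% throughout the range shown. If the end point is assessed at 24 months, as Table 2 has it, a 2-year look-back starts at enrolment and the carry-over largely disappears. Guideline-concordant status is also a legitimate end point in its own right.

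All of this stands against a stronger reading that a reader might infer: that the trial was powered for a different quantity and that over 85% is wrong. The protocol does not support that. Nor does its introductory remark that under 40% have undergone screening fix a carry-over rate, since it has no time window.

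What the reply does not remove is that, at 12 months and with the only interval given, pre-enrolment screens count, and women with such screens are not excluded.

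**Conclusion.** The point holds in a limited form. On the natural reading, the 12-month cervical component mixes new screening with screens that ARROW could not influence. Under the Step 2 model, a true 20-point gain in new screening would show as 18 points at 10% carry-over and 16 at 20%, at either ICC. The effect on power is conditional: material at ICC 0.05 if 20% v 40% describes uncovered women only, modest at ICC 0.03, and small if the 20-point gap holds across all women. The carry-over share, its equality across arms and the 2-year look-back are assumptions. The stated power is not shown to be in error. The improvement is cheap and worth making before the 12-month analysis, because enrolment in this cohort has closed and any lost precision cannot be regained with more women.

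**What to change.** 1. Derive a baseline flag, cervical screen in the 12 months before enrolment (yes or no), and enter it as a fixed covariate in the primary GEE model for this component, whether or not the arms look different. Flagged women are successes by definition under a 2-year look-back, so a logit link would give no finite coefficient for the flag. Fix in advance an identity link or a standardised risk difference, which also matches the threshold in percentage points.
2. Adjustment recovers precision but does not remove the dilution. Therefore prespecify, as a key analysis, screening done after enrolment among women not already covered at baseline. It could be made primary instead, but that changes the question and shrinks the denominator by the carry-over share.
3. State whether 20% and 40% mean new screening or up-to-date status, and restate the power if they mean new screening only.
4. Reconcile the 12-month time point in the end point section with the 24 months in Table 2, and apply the chosen one to items 1 to 3.

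The cost is end point wording, one derived variable and one prespecified analysis. Applying a 2-year look-back already requires reading the records that supply the flag.

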##### Cancer Treatment Cohort

The primary end point is the proportion of those who are adherent to cancer treatment (complete all treatment modalities as prescribed; 2-week delays will be allowed) at 12 months after diagnosis, the secondary end point is the proportion alive at 12 months after diagnosis, and the tertiary end point is the proportion with recurrence at 24 and 36 months (among those with 24- and 36-month follow-up).

For all the AYA living with HIV, we will report adherence to ART (proportion of those filling prescriptions at least every 3 to 6 months) and viral load at 12, 24, and 36 months. Viral load testing is generally conducted at least annually for AYA living with HIV as part of routine guideline-recommended practice. We will reinforce the need for regular viral load testing as part of health care provider training and have set aside funds to conduct viral load testing for study participants for whom this information is unavailable in the medical record.

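### Two of the three components of the early detection cohort's second primary end point depend on referral or diagnosis after randomisation, their denominator is not fixed, and the stated power covers only the first primary end point

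*Protocol article*

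**What the plan says.** Under Study End Points, Early Detection Cohort, the second of two primary end points has three parts:

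- Diagnostic follow-up, worded as "the proportion of those who complete the recommended follow-up supplemental or diagnostic procedures (within 3 months of receiving follow-up referral").
- Treatment initiation, worded as "those who initiate cancer treatment (within 3 months of diagnosis").
- Repeat visits, worded as "those who complete additional cancer detection visits over 36 months".

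Table 2 combines the first two in one row, "Proportion of participants completing diagnostic tests and initiating treatment in ≤90 d", with the specification "Measured as days from referral for testing and cancer diagnosis, respectively". The footnote that limits other Table 2 rows to people diagnosed with cancer is not attached to this row. Repeat examination and screening has its own row, read at 36 months.

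Under Sample Size and Recruitment, Early Detection Cohort, the calculation is said to rest on the dual primary end points, with a two-sided alpha of 0.025 for each and "allowing for the detection of an absolute 20% point improvement in the primary end points". The control rates given are 15% for physical examination and 20% for cervical cancer (CC) screening, both at 12 months. The powers given are over 90% and over 85%. No rate or power is given for any part of the second end point.

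Analysis of Hypotheses promises an intent-to-treat approach for the dual primary and the secondary end points. In introducing the secondary stage end point, the article also says: "We will likely have a few cancer cases in the study facilities".

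**The concern.** Examination and screening are the study's route to a referral, and a referral is the route to a diagnosis. ARROW exists to increase the first step. If diagnostic completion is analysed among the referred and treatment initiation among the diagnosed, the intervention has helped choose both denominators. The arms can then differ in who is counted even if ARROW does nothing to follow-up, and the difference can go in either direction.

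The article does not say which denominator applies, and neither choice gives what is claimed. The conditional denominator loses the randomised comparison. The all-enrolled denominator keeps it, but makes the 20-point threshold unrealistic at modest referral rates. An end point allotted its own alpha of 0.025 could therefore give a result that cannot be read as an effect of ARROW, while the sample size section tells the reader it was sized for.

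**Working it through.** **1. The plan's own power figures.** Inputs from the article: 9 facilities per arm, 200 participants each (100 women), 10% attrition, ICC 0.03 to 0.05, alpha 0.025 two-sided. This leaves m = 180 per facility, or 90 women.

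Effective n per arm = 9m / (1 + (m − 1) × ICC). Power = Φ[(d − z·SE0)/SE1], with z = 2.241, SE0 from the pooled rate and SE1 from the separate rates.

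| End point | ICC | Effective n per arm | Power |
|---|---|---|---|
| Examination, 15% v 35% | 0.03 | 1620/6.37 = 254 | 99.9% |
| Examination, 15% v 35% | 0.05 | 1620/9.95 = 163 | 97.6% |
| CC screening, 20% v 40% | 0.03 | 810/3.67 = 221 | 99.2% |
| CC screening, 20% v 40% | 0.05 | 810/5.45 = 149 | 94.0% |

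A t reference with 16 df lowers the two ICC 0.05 rows to 95.5% and 90.4%. The stated lower bounds hold for the first primary end point.

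**2. Selection in a referred-only comparison.** At the planned 12-month uptake, 1620 × 0.15 = 243 control participants and 1620 × 0.35 = 567 ARROW participants are examined. With the same referral rate in both arms, the ARROW referred group is 567/243 = 2.3 times larger.

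Suppose ARROW has no effect on follow-up. The 15% who attend in either arm complete at rate e, and the extra 20% who attend only under ARROW complete at rate h (e and h are assumed). Control then shows e, and ARROW shows (15e + 20h)/35.

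| e / h | Control | ARROW | Spurious difference |
|---|---|---|---|
| 80% / 60% | 80% | 68.6% | −11 points |
| 70% / 50% | 70% | 58.6% | −11 points |
| 80% / 50% | 80% | 62.9% | −17 points |
| 80% / 40% | 80% | 57.1% | −23 points |

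Per person enrolled, at 10% referral, the 80%/40% case reverses: 0.15 × 0.10 × 0.80 = 1.2% in control, against 0.10 × (0.15 × 0.80 + 0.20 × 0.40) = 2.0% in ARROW.

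**3. The all-enrolled reading.** At 10% referral (assumed), the most that could complete diagnostics after a physical examination is 0.15 × 10% = 1.5% in control and 0.35 × 10% = 3.5% in ARROW. Adding CC screening referrals, counted separately, gives 10% × (243 + 162)/1620 = 2.5% and 10% × (567 + 324)/1620 = 5.5%. Tripling these as a crude allowance for 36 months gives ceilings of 7.5% and 16.5%. Even the ARROW ceiling is below 20%.

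**4. Power for diagnostic follow-up among the referred.** Assumptions: completion 50% v 70%, alpha 0.025, 12-month uptake, examination and screening referrals added together (an upper count, since a woman may have both).

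| Referral rate | Referred, control v ARROW | Power, no clustering | Power, ICC 0.05 |
|---|---|---|---|
| 2% | 8 v 18 | 11% | 11% |
| 5% | 20 v 45 | 25% | 22% |
| 10% | 41 v 89 | 48% | 38% |
| 20% | 81 v 178 | 80% | 59% |
| 30% | 122 v 267 | 94% | 69% |

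If 36-month counts were two or three times the 12-month counts, a 10% referral rate would move to the 20% or 30% row.

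**5. Power for treatment initiation among the diagnosed.** Assumptions: 50% v 70%, alpha 0.025, cancers split equally between arms, no clustering. Totals of 10, 20 and 30 cancers give 5.2%, 8.7% and 12.6% with the pooled null variance, and 5.7%, 9.5% and 13.6% with the unpooled variance. For comparison, 90% power needs 147 per arm.

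**The case against.** The strongest reply is that the end point is not confined to people selected after randomisation. Additional detection visits depend on neither referral nor diagnosis and can be analysed in everyone enrolled. This stands: the fault lies in two components of three, and a reader should not infer that the whole end point is conditional.

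Next, the article never states a referred-only denominator. Table 2 says participants, and intent-to-treat is promised. This stands in part. Referred-only is the natural reading of windows that start at referral and diagnosis, but it is an inference. The defect is that the denominator is open, and step 3 shows that the literal Table 2 reading does not rescue the 20-point threshold at about 10% referral.

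Third, a reader might infer that the second end point as a whole falls far short of the stated power. The documents do not support this for diagnostic follow-up: they give no referral rate, the end point accrues over 36 months, and plausible counts reach 80-94% before clustering. It is fair for treatment initiation if cancers are few, as the article expects.

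A reader might also extend the criticism to early stage among those diagnosed and to "the proportion with recurrence at 24 and 36 months (among those with 24- and 36-month follow-up"). Neither adds much. The article already calls the stage findings inconclusive. The recurrence restriction is most naturally administrative, because some patients will have only 12 months of follow-up, and the end point is tertiary.

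Finally, the repeat-visit component has no stated control rate or power either, and it overlaps with the first primary end point. That is a real cost of relying on it.

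**Conclusion.** The point holds in this form. Two of the three components of the second primary end point can be met only after a post-randomisation referral or diagnosis that ARROW is designed to influence. Analysed among the referred or diagnosed, they do not give an intent-to-treat comparison. Analysed in all enrolled, they do, but a 20-point difference is out of reach unless referral is far more common than about 10% of those examined. The article does not choose between the two.

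The sample size statement claims to cover both primary end points but supports only examination and CC screening at 12 months, where it is sound.

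The spurious differences of 11 to 23 points show what is possible under assumed completion rates; they do not estimate the bias, and its sign depends on who the extra attenders are. Power for treatment initiation is about 5-14% with 10 to 30 cancers, an assumed range. Power for diagnostic follow-up cannot be settled from the documents. The selection problem does not shrink as numbers grow.

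**What to change.** 1. Define the confirmatory analysis of the second primary end point on all enrolled participants. Repeat examination and screening at the recommended interval, already a Table 2 row, allows this, with all enrolled women as denominator for the CC part.
2. Report diagnostic completion among the referred and treatment initiation among the diagnosed as descriptive, with numerators over all enrolled alongside. Use the same denominators in Table 2.
3. In the sample size section, state that the powers of over 90% and over 85%, and the 20-point threshold, apply to the first primary end point at 12 months only. Give a control rate and power for the second, or say that it was not sized for.

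The change uses data already planned for collection. With recruitment from June 2024 to February 2025, 36-month follow-up runs from about June 2027 to February 2028, so the definition can be fixed before those data mature. The cost is that the care-cascade proportions among the referred or diagnosed lose confirmatory status, although timely referral is part of the stated hypothesis, and the power claim covers less.
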